### 9.6.7 WELLBEING

**Outcome definition:** Treatment arm difference in i) SF-36 score, ii) Addi-QoL score from baseline to Day 120.

**Analysis:** The SF-36 is scored according to the RAND Corporation scoring instructions. Briefly, the responses to questions are individually awarded a weighted score and are grouped according to the domain assessed. The scores for questions from a given domain are averaged, and a final score for the domain is produced (from 0 – 100, higher scores indicating a more positive outcome). The 8 domains assessed by the SF-36 include: physical functioning, role functioning/physical, role functioning/emotional, energy/fatigue, emotional wellbeing, social functioning, pain, general health and health change. Each domain will be analysed individually.

PRED-AID Study Statistical Analysis Plan (SAP)

The Addi-QoL is a validated questionnaire containing 30 questions about wellbeing. Positive question responses are graded and weighted from 1 to 4, and negative question responses are graded from 4 to 1. The total score from the questionnaire will be between 30 and 120, with a higher value indicating a more positive outcome.

A multilevel repeated measures linear mixed effect model will be used to estimate the treatment arm difference in the above questionnaires, from baseline to Day 120. Similar to the primary analysis model, the model will include fixed effects for time (2 categories: Day 30 and Day 120), treatment arm (2 categories: prednisolone first and hydrocortisone first), period, type of AI, baseline measurement and use of a bone sparing agent. A random participant effect will be included and an unstructured covariance matrix will be used. The treatment effect at 120 days will be reported as a p-value with a 95% confidence interval. The models assumptions about random effects distributions, correlation structure and residuals will all be investigated. If any assumptions are poorly met then log transformation of the analyte in question, will be explored. If the mixed effect model including both 30 and 120 day outcomes fails to converge, treatment effects will be estimated using separate mixed linear regression models for each follow-up time point.

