## 6.2 TREATMENT ARMS

At randomisation, participants will be allocated to one of two treatment arms, to receive either prednisolone therapy first, or hydrocortisone therapy first:

- A) Prednisolone first: participants will receive four months of prednisolone and placebo tablets in the first Study Period and hydrocortisone in the second, four-month Study Period.
- B) Hydrocortisone first: participants will receive four months of hydrocortisone in the first Study Period and prednisolone with placebo tablets in the second, four-month Study Period.

The dose of the participant's usual regimen will be unchanged from their pre-study dose. The dose of the alternative medication to be used will be elucidated prior to each participant's randomisation on the study.

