## 9. STATISTICAL METHODOLOGY

### 9.1 GENERAL METHODOLOGY

Data will be collected and recorded throughout the study on both paper case record files and a validated database (Oracle InForm). Following last patient last visit and all data entry final data checks will be conducted. Post the resolution of any final data queries database lock will occur for analysis.

The main analysis will be conducted following the intention-to-treat principle and include all randomised patients, according to their randomised assignment for each period, irrespective of treatment actually received. A supplementary secondary per-protocol analysis will be performed for the primary outcome.

Since randomisation is stratified by type of AI (primary vs secondary) analyses of outcomes will involve adjustment for this factor, unless otherwise indicated. For continuous outcomes, baseline values of the outcome will also be adjusted for to increase power(9). For treatment period 1 the baseline outcome will be the outcome measured at the start of period 1. For period 2 the baseline should be from the assessments measure after the completion of period 1 and washout. This baseline definition will be applied to all analyses. Change from baseline will be calculated as post-baseline value – baseline value for the associated period.

Missing baseline covariate data are not anticipated since covariates must be recorded to allocate treatment. However, if there are missing values for baseline measure of a clinical outcome, they will be replaced by the mean of the observed baseline values for all participants in all treatment arms (mean imputation). This technique improves the statistical efficiency in the estimation of treatment effect and is justifiable since randomisation ensures that baselines are independent of treatment group(10).

Every effort will be made to obtain all follow up data for all participants, including those that have stopped treatment. All available data will be included within the analysis. The primary analysis model to be employed uses maximum likelihood estimation and is consequently efficient for handling missing outcome data under a MAR assumption. Where appropriate sensitivity analyses will be conducted to check that the conclusions are robust for, example, to the missing data assumption.

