#### **9.6 SECONDARY EFFICACY ANALYSIS**

##### **9.6.1 OTHER MARKERS OF BONE HEALTH**

## PRED-AID Study Statistical Analysis Plan (SAP)

**Outcome definition:** Treatment arm difference in i) P1NP, ii) BALP, iii) Corrected calcium, iv) PTH, v) Vitamin D, vi) NTX from baseline to Day 120.

**Analysis:** A multilevel repeated measures linear mixed effect model will be used to estimate the treatment arm difference for each of the above bone markers from baseline to Day 120. Similar to the primary analysis model, the model will include fixed effects for time (2 categories: Day 30 and Day 120), treatment arm (2 categories: prednisolone and hydrocortisone), period, type of AI (primary or secondary), baseline outcome, use of a bone sparing agent. A random participant effect will be included and an unstructured covariance matrix will be used. The treatment effect at 120 days will be reported with a 95% confidence interval. The models assumptions about random effects distributions, correlation structure and residuals will all be investigated. If any assumptions are poorly met then log transformation of the analyte in question, will be explored. If the mixed effect model including both 30 and 120 day outcomes fails to converge, treatment effects will be estimated using separate mixed linear regression models for each follow-up time point.

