#### 9.6.4 INFECTION RATES AND SEVERITY

**Outcome definition:** Treatment arm difference in the frequency of infections from baseline to Day 120.

**Analysis:** The GNCQ is a validated questionnaire that records the frequency of 6 different type of infections in the last 6 months (upper respiratory tract, lower respiratory tract, gastroenteritis, mucosal infections, lower urinary tract infections and flu). Respondents record either 0, 1, 2, 3, >3, or unknown frequencies of each type of infection.

The data will be tabulated and reported for each infection type at baseline and Day 120 for each treatment arm. McNemar-Bowkers test will be used to assess the change between treatment periods.

The data will also be weighted as follows: 0 or "don't know" will be scored as 0.5, 1-2 as 2, 3 or more as 4. The sum of the weighted scores will be treated as a continuous variable and a multilevel repeated measures linear mixed effect model will be used to estimate the treatment arm difference, from baseline to Day 120. Similar to the primary analysis model, the model will include fixed effects for time (2 categories: Day 30 and Day 120), treatment arm (2 categories: prednisolone and hydrocortisone), period, type of AI (primary or secondary), baseline weighted GNCQ, use of a bone sparing agent. A random participant effect will be included and an unstructured covariance matrix will be used. The treatment effect at 120 days will be reported with a 95% confidence interval. The models assumptions about random effects distributions, correlation structure and residuals will all be investigated. If any assumptions are poorly met then log transformation of the analyte in question, will be explored. If the mixed effect model including both 30 and 120 day outcomes fails to converge, treatment effects will be estimated using separate mixed linear regression models for each follow-up time point.

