#### 9.6.5 IMMUNOLOGY PROFILES

**Outcome definition:** Treatment arm difference in i) total white cells, ii) neutrophils, iii) lymphocytes, iv) eosinophils, v) basophils, vi) natural killer cells (including subtypes), vii) monocytes (including subtypes) viii) soluble immunological analytes; from baseline to Day 120.

**Analysis:** A multilevel repeated measures linear mixed effect model will be used to estimate the treatment arm difference in the above immunological markers, from baseline to Day 120. Similar to the primary analysis model, the model will include fixed effects for time (2 categories: Day 30 and Day 120), treatment arm (2 categories: prednisolone and hydrocortisone), period, type of AI (primary or secondary), baseline weighted GNCQ, use of a bone sparing agent. A random participant effect will be included and an unstructured covariance matrix will be used. The treatment effect at 120 days will be reported with a 95% confidence interval. The models assumptions about random effects distributions, correlation structure and residuals will all be investigated. If any assumptions are poorly met then log transformation of the analyte in question, will be explored. If the mixed effect model

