### 9.6.6 SAFETY

**Outcome definition:** Treatment arm difference in i) FBC, ii) renal profile, iii) LFTs, iv) CK, v) ACTH, vi) CBG, vii) Bicarbonate viii) number of reports of myopathic symptoms, or nausea; from baseline to Day 120.

**Analysis:** A multilevel repeated measures linear mixed effect model will be used to estimate the treatment arm difference in the above safety outcomes (except (viii)), from baseline to Day 120. Similar to the primary analysis model, the model will include fixed effects for time (2 categories: Day 30 and Day 120), treatment arm (2 categories: prednisolone and hydrocortisone), period, type of AI (primary or secondary), baseline outcome. A random participant effect will be included and an unstructured covariance matrix will be used. The treatment effect at 120 days will be reported as a p-value with a 95% confidence interval. The models assumptions about random effects distributions, correlation structure and residuals will all be investigated. If any assumptions are poorly met then log transformation of the analyte in question, will be explored. If the mixed effect model including both 30 and 120 day outcomes fails to converge, treatment effects will be estimated using separate mixed linear regression models for each follow-up time point.

Data for symptom reporting will tabulated according frequency of reported symptoms will be presented at baseline and Day 120 for each treatment arm. McNemar's test will be used to assess the change between time periods.

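### The SAP's wellbeing model (9.6.7) codes treatment as the randomised sequence, so its SF-36 and Addi-QoL coefficient is not the prednisolone–hydrocortisone contrast; a lesser slip in 9.6.5 gives the immunology models the wrong baseline covariate.

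*Combined protocol and SAP*

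**What the plan says.** **Wellbeing.** SAP 9.6.7 fits a repeated measures mixed model with "treatment arm (2 categories: prednisolone first and hydrocortisone first), period, type of AI". The remaining terms are time point, the baseline measurement, use of a bone sparing agent and a random participant effect. The Day 120 treatment effect is to be reported with a p-value and a 95% confidence interval.

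SAP 6.2 says what the first level means: "Prednisolone first: participants will receive four months of prednisolone and placebo tablets in the first Study Period and hydrocortisone in the second" period. The second level is the reverse order.

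**The other secondary models.** SAP 9.6.1 to 9.6.6 name the two drugs as the levels: "treatment arm (2 categories: prednisolone and hydrocortisone". The safety model in 9.6.6 is typical, with drug coding and the outcome's own baseline: "treatment arm (2 categories: prednisolone and hydrocortisone), period, type of AI (primary or secondary), baseline outcome".

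**Immunology.** SAP 9.6.5 codes treatment by drug but lists "type of AI (primary or secondary), baseline weighted GNCQ, use of a bone sparing agent". The same covariate string stands in the infection model (9.6.4), where the weighted GNCQ score is the outcome and the covariate belongs.

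**General rules.** SAP 7.1 and 9.1 analyse participants by the treatment randomised for each period. SAP 9.1 adds: "For continuous outcomes, baseline values of the outcome will also be adjusted for to increase power". It also applies the primary outcome's modelling approach to continuous secondary outcomes. The primary model in 9.5 has treatment, period and baseline osteocalcin.

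**The concern.** In a two-period crossover everyone takes both drugs, and the order is what is randomised between participants. A factor that separates the two orders compares groups of people who have each had one period on each drug. It can pick up carry-over or chance differences between the groups. It does not pick up the drug difference, which lies within participants.

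SF-36 and Addi-QoL are the trial's patient-reported comparison of the two drugs, and protocol 1.2 expects equivalent outcomes. A coefficient that sits near zero because of its coding says nothing for or against that expectation.

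The carry-over check is also affected if it is run on these outcomes. SAP 9.1 tests carry-over by adding a treatment-by-period interaction. With treatment coded as sequence, that interaction is the drug effect (shown in the working), so a real drug difference would be labelled carry-over.

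The immunology slip is of a different kind. The drug contrast is still the one being estimated, but the covariate that 9.1 includes to gain power has been replaced by an infection-questionnaire score.

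**Working it through.** **1. The plan's own figure.** Inputs from SAP 6.7: 44 completers, effect 1.5 µg/L, SD 3.0, correlation 0.5, two-sided 5%, 20% drop-out.

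- SD of the within-participant difference: 3.0 × √(2 × (1 − 0.5)) = 3.0.
- Non-centrality: 1.5 × √44 / 3.0 = 3.32. Noncentral-t power is 90.0% on 43 df and 89.97% on 42 df.
- Recruitment: 44 / 0.8 = 55.

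The stated power and sample size reproduce. They concern osteocalcin, whose model has a treatment term and its own baseline, so this point leaves them unchanged. The documents give no power for wellbeing or immunology.

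**2. Sequence coding with complete data.** Let τ be the prednisolone-minus-hydrocortisone effect and π the period effect, with no carry-over (SAP 9.5 does not expect any). Expected means, apart from a constant:

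| Sequence | Period 1 | Period 2 | Mean |
|---|---|---|---|
| Prednisolone first | τ | π | (τ + π)/2 |
| Hydrocortisone first | 0 | τ + π | (τ + π)/2 |

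- Sequence contrast: (τ + π)/2 − (τ + π)/2 = 0 for any τ.
- Sequence-by-period interaction: (π − τ) − (τ + π − 0) = −2τ. In this coding the drug effect appears only here, and 9.6.7 has no such term.

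**3. With 20% lacking period 2.** Take 22 participants per sequence in period 1 and 22 × 0.8 = 17.6 in period 2. The contrast between sequences is +τ in period 1 and −τ in period 2. Least squares weights these by numbers: (22 − 17.6) / (22 + 17.6) × τ = 4.4/39.6 × τ = 0.11τ. A mixed model weights participants differently. For a random intercept with within-participant correlation ρ the fraction is 0.2 / (0.2 + 0.8 × 2/(1 + ρ)), which is 0.11 at ρ = 0 and 0.16 at ρ = 0.5. It stays a small fraction of τ.

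**4. With differential carry-over.** A carry-over of 0.4 in one sequence, complete data, gives a coefficient of 0.4/2 = 0.20 whatever τ is. The coefficient is then carry-over and still not the drug effect.

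**5. Simulation.** 44 participants, two periods, Days 30 and 120, own period baseline, outcome SD about 1, no carry-over, 150 runs per row:

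| True τ | Period 2 missing | Sequence coding: mean, rejection | Drug coding: mean, rejection |
|---|---|---|---|
| 0 | none | 0.02, 5% | 0.00, 8% |
| 0.5 | none | 0.02, 5% | 0.50, 90% |
| 1.5 | none | 0.02, 1% | 1.50, 100% |
| 0.5 | 20% | 0.07, 10% | 0.52, 92% |
| 1.5 | 20% | 0.18, 9% | 1.51, 100% |

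The Monte Carlo standard error of the means is about 0.02 for sequence coding and 0.01 for drug coding. The simulation used participant and participant-by-period random effects, not an unstructured residual matrix. The zero in step 2 is algebra and does not depend on that choice.

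**6. Immunology precision.** The documents give no correlations for these markers, so these are assumptions. Let w be the baseline–outcome correlation within a period and c the correlation of any two measurements across periods. The period differences of outcome and baseline then correlate at r = (w − c)/(1 − c). The variance of the change-score contrast is proportional to 2(1 − r) without the own baseline and to 1 − r² with the best adjustment for it. The standard-error ratio is √(2/(1 + r)).

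- w = 0.9, c = 0.3: r = 0.857, ratio 1.04.
- w = 0.7, c = 0.5: r = 0.4, ratio 1.20.
- w = c: r = 0, ratio 1.41.

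Simulated mixed models with all correlations equal gave 1.40 at 0.3, 1.29 at 0.5 and 1.11 at 0.8, inside this range. If the raw value is modelled and all correlations are equal, r = 0 and the own baseline explains none of the within-participant difference. With the SAP 6.7 values the standard error is then √(9/44) = 0.452 with or without it.

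**The case against.** The best defence is that the SAP already contains the right model. Sections 7.1 and 9.1 assign treatment by period, 9.1 requires the outcome's own baseline and carries the primary approach over to continuous secondary outcomes, and 9.5 shows that approach. Section 9.6.7 describes its own model as similar to the primary one and asks for a treatment effect at 120 days, which a sequence term cannot supply. An analyst who followed the general rules would fit the correct model. SAP 9.4 also describes secondary outcomes by arm, period and time point, so a real wellbeing difference would be visible beside a coefficient near zero.

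This stands as evidence that both wordings are slips. It does not remove the contradiction. SAP 6.2 itself uses treatment arm to mean sequence, and the bracketed levels in 9.6.7 are the specific instruction to the programmer. It is the only secondary model whose levels are the sequences.

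Some stronger readings are tempting and are not supported:

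- *The coefficient is zero whatever the drugs do.* This holds in expectation only with complete data and no differential carry-over. The plan allows 20% drop-out and analyses all available data.
- *The immunology estimates are biased, or lose a fixed share of precision.* The drug contrast there stays randomised and unbiased. A single figure such as 28% (simulated standard errors 0.628 against 0.490) needs a correlation of 0.5 between every pair of measurements. SAP 6.7 gives 0.5 for osteocalcin across periods only.
- *A null wellbeing analysis was intended, or would certainly be taken as equivalence.* Nothing in the documents shows intent, and the second step assumes that the slip survives programming and review.

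**Conclusion.** The point holds for wellbeing. As written, the 9.6.7 model does not estimate prednisolone versus hydrocortisone. Its coefficient has expectation 0 under complete data and no differential carry-over, and about 0.11 of the drug effect by least squares if 20% lack period 2. In simulation it rejected in 1% to 10% of runs, against 90% or more with drug coding at the same non-zero effects. This is a wrong rule contradicted elsewhere in the SAP, and it should be corrected before unblinding.

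The immunology covariate in 9.6.5 is also wrong against 9.1, but minor. It may cost precision only: a standard error roughly 1.04 to 1.4 times larger for a change score, under correlations that are assumed here (cross-period no higher than within-period), and possibly nothing if raw values are modelled. Section 9.6.5 does not say which of the two is the dependent variable.

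Only secondary outcomes are touched. The primary analysis and the sample size of 55 are unaffected.

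**What to change.** In SAP 9.6.7, give the treatment factor the levels prednisolone and hydrocortisone, defined as the drug assigned in that period, as in 9.6.1 to 9.6.6. If the carry-over check is run on wellbeing, use the same coding there.

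In SAP 9.6.5, replace the weighted GNCQ covariate with the baseline value, for that period, of the marker being analysed.

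The cost is two wording corrections. They need no new data, no change in sample size and no change to the primary analysis. Made before unblinding, they avoid a post hoc departure from the SAP.

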#### 9.6.8 COMPLIANCE TO REGIMEN

**Outcome definition:** Treatment arm difference in the number of tablets returned between Day 120 of each treatment period.

**Analysis:** The number of tablets returned by each patient at the end of each treatment period will be counted and recorded. The number of tablets expected back will be calculated from the patients dosing diary, number of tablets dispensed, and any known losses of tablets reported by the patient. The difference between the expected number of tablet and actual number of tablets received will correspond to the number of missed doses.

The number of missed doses in each treatment period will be tested for normality using the Shapiro-Wilk test. If the assumption of normality is not met, then a log transformation will be explored. A paired t-test will be used to assess the mean difference in missed doses between treatment periods. Where the data is non-parametric, a Wilcoxon test will be used.

#### 9.7 SAFETY ANALYSIS

A safety set (SS) population, consisting of all participants who received at least one dose of the assigned intervention, will be defined for describing adverse events in. Adverse events will be summarised by type (AE or SAE) and treatment arm in a given period. AEs will be tabulated by treatment group for both the number of events and the number of participants with the type of event in a given period. A listing will be produced detailing all Serious Adverse Events (SAEs). Only descriptive analysis of safety will be performed, no formal statistical testing is planned.

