### Methods of data collection and analysis

Data will be collected and recorded throughout the study on both paper case record files and a validated database (Oracle InForm). Following last patient last visit and all data entry final data checks will be conducted. Post the resolution of any final data queries database lock will occur for analysis.

The analysis will follow the intention-to-treat principle and include all available data from participants within the treatment sequences to which they were randomised, regardless of treatment subsequently received.

As this is a two-period two-treatment crossover trial, the treatment effect will be estimated using a linear mixed effect model with participant as a random effect and fixed effects for treatment

and period, type of AI (primary vs secondary). Model assumptions, including the normality of residuals and random effects distributions will be assessed. If any assumptions are poorly met, then an appropriate transformation of the outcome (e.g. log transformation) will be considered.

Every effort will be made to obtain all follow up data for all participants, including those that have stopped treatment. The analysis method employs maximum likelihood estimation and is thus efficient for handling missing outcome data under a missing at random (MAR) assumption. Where appropriate sensitivity analyses will be conducted to check that the conclusions are robust for, example, to the missing data assumption. Although a washout period is incorporated into the design of the study to minimise carry-over effects, we will assess whether there is any evidence of a carry-over effect by fitting a separate linear mixed model which further includes the treatment by period interaction.

The continuous secondary outcomes will be analysed using the same modelling approach as specified above for the primary outcome. Where there are repeated measures of an endpoint within each period, we will display the effects over time and choose further appropriate statistical methods to assess any differences in the patterns over time. We will report compliance to study drug using data for pills missed doses over the study period. Adverse events will be tabulated by treatment group and period.

All treatment effect estimates will be reported with 95% confidence intervals and a two-sided 5% level of significance will be used. A detailed statistical analysis plan will be drawn up and agreed by the TSC prior to any unblinded data extraction.

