#### **4. INTRODUCTION/STUDY SUMMARY**

Steroid replacement therapy is vital for the health of patients with adrenal insufficiency (AI), who are unable to produce the natural stress hormone, cortisol. The objectives of steroid replacement therapy are to replace the body's physiological requirements for cortisol without over-replacement and consequent Cushing's syndrome. Equally, under-replacement presents the risk of patients experiencing potentially fatal Addisonian crises(1). Appropriately replacing a patient's steroid requirement is a significant challenge(2).

Hydrocortisone is used in the majority of patients with AI in the UK(3). However, hydrocortisone has a short duration of action, necessitating dosing 3 times a day(4). Low-dose prednisolone is an alternative to hydrocortisone which needs only once-daily. There have been no studies directly comparing low-dose prednisolone to hydrocortisone treatment.

Using a two-arm, two-period, double-blind randomised crossover study design, this study aims to compare the effects of two routine treatments of AI, low dose prednisolone and standard regimens of hydrocortisone. The primary outcome will be bone health. Secondary outcomes include: Cardiovascular risk, Glycaemic control, Infection rates and severity, Immunology profiles, Adverse events and Adverse Reactions, Wellbeing and Compliance

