#### **5. STUDY OBJECTIVES**

##### **5.1 PRIMARY OBJECTIVE**

To evaluate and compare the safety and efficacy of low dose prednisolone and hydrocortisone treatments for the management of AI.

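### SAP 9.7 gives adverse events no by-drug summary over both periods, no within-participant comparison and no interval, and does not tabulate the adverse reactions named as an outcome

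*Combined protocol and SAP*

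**What the plan says.** The SAP states its primary objective as "To evaluate and compare the safety and efficacy of low dose prednisolone and hydrocortisone treatments for the management of AI" (SAP 5.1). The primary outcome is bone health. SAP 4 lists the secondary outcomes, among them "Immunology profiles, Adverse events and Adverse Reactions, Wellbeing and Compliance".

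For AEs, SAP 9.7 says: "Adverse events will be summarised by type (AE or SAE) and treatment arm in a given period". It then says: "AEs will be tabulated by treatment group for both the number of events and the number of participants", again within a given period. It adds a listing of all SAEs and closes with: "Only descriptive analysis of safety will be performed, no formal statistical testing is planned". Protocol section 9 (Methods of data collection and analysis) is shorter: "Adverse events will be tabulated by treatment group and period". Neither document promises a total by drug over both periods, a count of participants with an event on one drug but not the other, or an interval.

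SAP 8.3 says that SUSARs will be recorded for each period alongside AEs and SAEs. Protocol 7.2 has the investigator assign causality in six categories.

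Other safety data are treated differently. SAP 9.6.6 fits mixed models with a random participant effect and terms for treatment and period to the laboratory safety variables, and says: "The treatment effect at 120 days will be reported as a p-value with a 95% confidence interval". It compares reports of myopathic symptoms or nausea with McNemar's test.

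**The concern.** Every participant is meant to take both drugs, so the trial can ask of each person whether an event occurred on prednisolone, on hydrocortisone, on both or on neither. A table by arm within one period compares different people, about 22 against 22 of the 44 completers. Two such tables, with no total, estimate or interval, leave readers to form their own impression, and similar-looking counts may be taken as similar safety.

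The pairing cannot be worked out from the planned counts, so a reader of the report could not repair the gap later. Adverse reactions, the subset of AEs judged causally related to a drug, are a named outcome with no planned output. Finally, the sentence on descriptive analysis, if taken to cover all safety data, conflicts with the p-values and McNemar's test in 9.6.6.

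**Working it through.** **The plan's own figure.** SAP 6.7 gives SD 3.0, correlation 0.5, a difference of 1.5 µg/L, two-sided 5% and 90% power. The SD of the within-person difference is 3.0 × √(2 × (1 − 0.5)) = 3.0. The normal approximation gives n = (3.0 × (1.960 + 1.282) / 1.5)² = 42.0, so 43. The paired t calculation gives 44 with power 90.0%, and 44 / (1 − 0.20) = 55. The sample size reproduces and is not in dispute. Only the 44 completers are carried forward.

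**Assumptions.** The documents give neither an AE rate nor a within-person correlation for AEs. I take the proportion with at least one event as p = 10%, 30% or 50% on each drug, correlation φ = 0, 0.3 or 0.5, and 22 completers per sequence.

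**Formulas for the 95% half-width of the risk difference between drugs.**
- One period alone, 22 v 22: 1.96 × √(2p(1 − p) / 22)
- Both periods added, pairing ignored, 44 v 44: 1.96 × √(2p(1 − p) / 44)
- Both periods, paired: 1.96 × √(2p(1 − p)(1 − φ) / 44)

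At p = 30%, 2p(1 − p) = 0.42:
- one period: 1.96 × √(0.42 / 22) = 0.271
- both periods added: 1.96 × √(0.42 / 44) = 0.191
- paired, φ = 0.3: 1.96 × √(0.42 × 0.7 / 44) = 0.160
- paired, φ = 0.5: 1.96 × √(0.42 × 0.5 / 44) = 0.135

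| Assumed risk | One period | Periods added (same as paired, φ = 0) | Paired, φ = 0.3 | Paired, φ = 0.5 |
|---|---|---|---|---|
| 10% | ±18 | ±12.5 | ±10.5 | ±9 |
| 30% | ±27 | ±19 | ±16 | ±13.5 |
| 50% | ±29.5 | ±21 | ±17.5 | ±15 |

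The first step, ±27 to ±19, comes from adding the periods. Only the second, ±19 to ±16 or ±13.5, comes from pairing.

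**Whether the planned counts hold the paired result.** Suppose 15 of 44 have an event on one drug and 22 of 44 on the other. These totals fit several splits of the discordant participants:

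| Both | First drug only | Second drug only | Neither | Exact McNemar p |
|---|---|---|---|---|
| 14 | 1 | 8 | 21 | 0.039 |
| 11 | 4 | 11 | 18 | 0.12 |
| 7 | 8 | 15 | 14 | 0.21 |

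Fisher's test, which sees only the totals, gives p = 0.19 in all three cases. The p-values only show that the same totals carry different within-person evidence; they are not a request for AE tests.

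**The case against.** Much of the case on the other side stands.

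- A reader might infer that the pairing is discarded for safety as a whole. SAP 9.6.6 does not support that: the laboratory variables are modelled with a participant effect, and McNemar's test is a paired test. It leaves the AE gap open, because the test covers only myopathic symptoms and nausea, does not adjust for period, and does not say clearly whether it contrasts drugs, periods, or baseline with Day 120.
- A reader might infer from SAP 5.1 that AEs need formal testing. Safety is a secondary outcome and nothing is powered on AEs. Protocol section 9 says "All treatment effect estimates will be reported with 95% confidence intervals", but that concerns treatment-effect estimates, and none is planned for AEs. Descriptive reporting is a legitimate choice.
- A reader might take ±27 against ±13.5 as the cost of lost pairing. It is not. Each participant takes each drug in one period, so anyone can add arm A period 1 to arm B period 2 and reach about 44 v 44. For the same reason, how often a single period table would mislead is not a fair measure of the plan.
- A reader might infer that SUSARs go unreported. A SUSAR is serious by definition (protocol 7.1), so it falls within the SAE rows and the listing.
- A reader might argue that unrelated events will swamp the drug reactions. No figure in the documents supports this, and protocol 7.2 expects most events to be treatment-related.
- In context, the descriptive-only sentence in 9.7 probably means AEs. The conflict with 9.6.6 is one of wording.
- A paired table has its own weakness. Protocol 4.4 allows withdrawal for significant AEs, and the plan allows for 55 × 0.20 = 11 drop-outs. Participants who leave in period 1 would be absent from a table limited to those exposed to both drugs.

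**Conclusion.** The point holds for AEs, SAEs and adverse reactions. SAP 9.7 leaves the comparison of AEs between the drugs less precise than the crossover allows, and it omits adverse reactions, which SAP 4 names as an outcome. This is a low-cost improvement to the AE reporting; it has no bearing on the primary analysis.

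The size rests on assumed rates. At 30% risk with 44 completers, a total over both periods takes the half-width from ±27 to ±19 points, and pairing takes it to ±16 or ±13.5 only if the correlation is 0.3 or 0.5. If events on the two drugs are uncorrelated within a person, pairing gains nothing and the benefit is that of the by-drug total and its interval. What does not depend on these assumptions is that the planned counts cannot show who had events on one drug only, and that adverse reactions have no planned table.

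**What to change.** In SAP 9.7:

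1. Keep the by-period tables. Add totals by drug over both periods for the whole safety set, as events and as participants, with the number exposed to each drug as denominator.
2. Add a four-way within-participant table: event on prednisolone only, hydrocortisone only, both, neither. Report a period-adjusted risk difference with a 95% confidence interval, without a p-value and labelled exploratory. Preferably estimate it from a model with drug and period terms that allows for repeated observations and uses every exposed participant. Report separately the AEs of those exposed to only one drug.
3. Add a row by drug for adverse reactions, stating which causality categories of protocol 7.2 count as a reaction, and flag SUSARs within the SAE rows. Protocol 7.3.2 puts causality on the SAE form. Protocol 7.3.1 does not list the fields for non-serious events, so check that the case report form holds causality for them.
4. Limit the no-testing sentence to adverse events, so that it agrees with 9.6.6.

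The cost is some SAP wording and one extra table, with no new visits or assessments. Intervals for rare events will be wide. The paired table may be selective if participants withdraw for AEs in period 1, which is why the whole-set totals and the separate report in steps 1 and 2 are needed.
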